## Methods and analysis

This study will involve primary data collection of cross-sectional data that will be analysed using a ‘production function’ approach in which care outcomes (eg, social care-related QoL) are modelled as resulting from care inputs (eg, hours of care per week) and other observable factors.^13 14^

The attribution of causal effects is a challenge, as observed levels and types of care services (ie, the treatment) are dependent on both observable factors as well as factors that cannot be observed or measured; see Gousia *et al*^11^ for a review. Unobserved factors can deviate the study findings from the truth. Randomised control trials (RCTs), in which participants are randomly assigned to prespecified and controlled treatments, are considered the *gold standard* in the economic evaluation of health interventions. The adequate use of randomisation addresses this issue by balancing for observed and unobserved confounders between intervention and control groups.^26^

RCTs have been used in LTC to assess the effectiveness of smaller interventions (eg, home adaptations). For example, using the fact that people referred for the provision of an accessible showering facility by their local authority were usually put on waiting lists (control group), Whitehead and colleagues^27^ designed an RCT by randomly assigning people to receive the adaptation through a fast-tracked process (treatment group).

RCTs are, however, not always feasible or the most appropriate methodology in LTC care due to research ethics as well as internal and external validity considerations. For example, for assessing the comparative cost-effectiveness for domiciliary care by level of care need, we would have to randomly assign packages of different care intensities to people with different levels of care needs, which would be unethical. On the other hand, randomly assigning people with similar care needs to different models of care delivery would not only go against the personalisation approach in LTC in England (mandated by the Care Act 2014) but may also affect the RCT’s internal validity. People usually have strong preferences about their care, and their care arrangements can affect their QoL (eg, control over daily life is one of the domains assessed by the Adult Social Care Outcomes Toolkit (ASCOT)). Moreover, due to the complex and continuing nature of LTC, experimental settings often differ from routine practice, with substantial limitations to external validity.

An alternative approach, known as ‘instrumental variables’ (IV), has been successfully applied with observational data in LTC contexts.^13 14^ This addresses the potential issue of non-random selection (ie, we only observe the level and type of care that people have chosen or have been allocated by their local authority). We adopt the IV approach in this study. This is described in more detail in the ‘Data analysis’ section.

### Data requirements

The selected primary *care outcome* measure for people accessing care and for their unpaid carers is the ASCOT interview version (ASCOT-INT4; Netten *et al*; Malley *et al*; Malley *et al*^28^,^30^) and ASCOT-Carer INT4,^31^ respectively. These are validated instruments capturing domains of QoL that are relevant and important to adults accessing LTC services and their carers. The domains were developed based on evidence from qualitative interviews, focus groups and literature review of studies with adults accessing care and their carers to understand people’s views and perspectives on the most important areas of QoL affected by LTC.^28 31 32^ This concept/construct is known as social care-related QoL, which has been found to be sensitive to differences in satisfaction, quality and intensity of care.^33^,^36^ ASCOT has been identified as suitable and recommended for use in economic evaluation of LTC^37^ and is one of two outcome measures recommended by the National Institute for Health and Care Excellence (NICE) guidelines in LTC.^38^ An additional benefit of the use of ASCOT INT4 is that it allows the counterfactual self-estimation of the QoL effect of LTC services, as the difference between the current QoL and the ‘expected’ QoL in the hypothetical situation of absence of services.^30^

In addition to ASCOT, we will also collect data on other outcome measures. This includes potentially avoidable hospitalisations to capture the effects of homecare on avoidance of safety incidents or adverse health outcomes linked to increased demand on the NHS. For carers, we also collect data on self-reported health and employment outcomes.

Information on *care inputs* will be collected using questions on the participants’ use of paid domiciliary care (ie, hours of care per week) and other community-based care services (eg, day care, meals at home, support groups), as well as unpaid care (ie, hours of unpaid care per week).

We will also collect information on factors likely related to both care intensity and care outcomes, namely confounders. These include individual and household characteristics like age, gender, ethnicity, underlying health issues, difficulties with performing activities of daily living (ADLs), household composition, financial situation, the availability of home adaptations and general housing conditions and access to the local area and facilities. In addition, we collect information about the characteristics of the care recipients’ registered care location, namely type of service, sector and ownership; size; staffing levels; pay and employment conditions; characteristics and needs of people supported and commissioning practices of the local authorities they have contracts with, as well as the latest Care Quality Commission rating and date.

To reduce costs and avoid duplication, data on care home residents will come from the *Developing Resources and Minimum Data Set for Care Homes’ Adoption* (DACHA) study (NIHR127234). The design of survey questionnaires for this study has been informed (among others) by the structure of the data and variables collected in the DACHA project to make sure they are aligned for the comparative cost-effectiveness analysis between homecare and residential care. For example, the DACHA dataset includes information on care home residents’ QoL (collected using ASCOT Proxy), residents’ individual characteristics and care needs (eg, ADLs) and care home characteristics. The dataset includes a sample of about 679 residents from 34 care homes in England.^33^

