**Methods and analysis:**

This will be a cross-sectional study based on surveys of care recipients, their unpaid carers as well as formal care providers. In the first half of 2026, we will survey 1850 people accessing domiciliary care either through a homecare agency, a housing with care scheme or by directly employing personal assistants and 400 unpaid carers, all based in England. We will conduct a cost-effectiveness analysis taking a ‘production function’ approach and use quality of life as measured by the Adult Social Care Outcomes Toolkit as the main outcome of interest.

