### Recruitment of study participants

We will recruit people who access domiciliary care by using two different approaches, based on (1) whether people access care through a homecare agency or housing with a care setting or (2) whether people directly employ a PA.

For people accessing care via a homecare agency or housing with care setting, we intend to recruit 1050 participants through their registered care location. Care locations are recruited with the help of study stakeholders, including the Homecare Association, Housing LIN, NIHR Regional Research Delivery Networks, Skills for Care and the Care Quality Commission. We aim to recruit approximately 100 homecare agencies and 50 housing with care sites across England, ideally clustered in about 30 local authorities across four regions: Yorkshire and the Humber, East Midlands, West Midlands and the South East. The care provider recruitment was initiated in May 2025. We will collect key provider characteristics through a short online survey completed by managers of care locations registering to participate in the study in November 2025 to January 2026. We will distribute survey packs to their clients in February 2026. Based on previous work, we expect around 800 responses from people accessing care via a homecare agency and 250 responses from housing with care residents.

With respect to care recipients directly employing PAs, we intend to recruit 800 participants. Recruitment will take place through Mark Bates, a specialist insurance company that holds contact details of a large number of PA employers. This approach is successfully used by Skills for Care, one of our study partners, for their annual survey of PAs and PA employers. Survey packs will be sent to approximately 17 500 PA employer email addresses.

Participants who access domiciliary care will be asked to involve their unpaid carers, should they have such support. Not all participants will have unpaid care support, and some unpaid carers may not wish to participate. Based on previous studies that adopted the route of recruiting carers via adults with care and support needs, we (conservatively) anticipate collecting responses from approximately 400 unpaid carers.^39^

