### Inclusion criteria

Care recipients must be adults (ie, 18 years or over), accessing domiciliary care through a homecare agency or housing with care scheme (eg, extra care housing) or by employing a PA in England. Unpaid carers must be adult family members, partners or friends supporting a care recipient participating in the study.

All participants must have the mental capacity to consent. Our approach to mental capacity is informed by the following Mental Capacity Act principles: (1) every adult has the right to make decisions for themselves, and it must be assumed that they are able to make their own decisions unless it has been shown otherwise and (2) every adult has the right to be supported to make their own decisions. All reasonable help and support should be given to assist a person to make their own decisions and communicate those decisions before it can be assumed that they have lost capacity.

Our intention is to be as inclusive as possible in relation to people’s abilities and needs; however, we will instruct care providers to exclude people who lack the mental capacity to consent, based on their records of LTC assessment, having a court-appointed deputy or being under a Deprivation of Liberty Safeguard. We will also exclude PA employers who have an additional nominated adult (eg, a legal guardian) on their employer liability insurance.

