### Cost-effectiveness

The estimated impact of formal care input on QoL can be seen as the marginal change in utility (ie, marginal utility $u_{k}$) arising from a marginal change in formal care input k. Care input can be measured as cost-weighted services (eg, hours of home care multiplied by gross unit costs $c_{k}$), allowing the estimation of incremental cost-effectiveness ratios, as marginal costs per marginal utility ($c_{k}/u_{k}$). Incremental cost-effectiveness ratios can be compared between different levels of care intensity, with lower values representing greater efficiency (ie, better value for money). This is relevant for informing policy questions, such as how much potential gain additional funding can achieve or how best to allocate limited budgets across different alternative services.

We also position unpaid carers as beneficiaries of care and consider the cost-effectiveness of LTC services for unpaid carers. This expands the literature on the ‘spillover effects’ of LTC services on carers to consider that services can be targeted ‘at’ or ‘for’ carers and/or jointly for supported people and their carers, based on the whole family (sometimes, known as the ‘dyadic’) approach. See the next section for more details.

Additional considerations that would generalise cost-effectiveness implications are on the interdependency between the health and LTC systems. Existing research has explored, for example, the impact of LTC spending on health service use,^44^ and our stakeholder consultation also revealed an interest in these associated effects. We will assess the effects of LTC provision on avoidable hospitalisations (ie, effects on demand for healthcare) in the analysis. However, we gave these aspects less focus, as we regard them as additional to the main aims of LTC, which is to improve the social care-related QoL of care recipients and their carers.

Differential effects between care alternatives (eg, modes of domiciliary care or care settings) will be captured by the coefficient of the (binary) ‘treatment’ variable (eg, the setting or mode of interest over an alternative) in the matching models. These coefficients will provide the average difference between the ‘treated’ groups’ actual QoL and their QoL if they would have received the alternative type of care (ie, the average treatment effect on the treated).

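### Avoidable hospitalisations are seen only in people still alive, in domiciliary care and able to consent at the survey, so the estimated effect on healthcare demand can be biased in either direction

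*Protocol article*

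**What the plan says.** The Abstract gives the design: "This will be a cross-sectional study based on surveys of care recipients, their unpaid carers as well as formal care providers". The opening of Methods and analysis repeats it: "This study will involve primary data collection of cross-sectional data that will be analysed using a ‘production function’ approach".

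Inclusion criteria limits care recipients to adults "accessing domiciliary care through a homecare agency or housing with care scheme (eg, extra care housing) or by employing a PA in England", and adds: "All participants must have the mental capacity to consent". Recruitment of study participants fixes the sampling time for care locations: "We will distribute survey packs to their clients in February 2026". Direct employers of personal assistants (PAs) are reached by email through an insurer's contact list.

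Data requirements lists hospital admissions among the further outcomes: "This includes potentially avoidable hospitalisations to capture the effects of homecare on avoidance of safety incidents or adverse health outcomes". The Cost-effectiveness section says how they will be used: "We will assess the effects of LTC provision on avoidable hospitalisations (ie, effects on demand for healthcare) in the analysis". Aims and objectives makes the same commitment as part of the broader societal impact. The Cost-effectiveness section also says that these aspects receive less focus than social care-related quality of life.

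The Data analysis section uses an instrumental variable for selection into care intensity on unobserved factors, and matching for selection between settings or modes of care.

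**The concern.** Admission is an event before the survey, but it can be recorded only for people who are in the sampled population afterwards. A person whose admission ended in death, a stay still continuing at the survey, a move to a care home or loss of capacity is not there to be counted. Whether a person is back at home and in the service plausibly depends on the care available there. Inclusion in the sample may then depend on both the exposure (care level) and the outcome (admission).

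At stake is the reading of the hospitalisation result. The Discussion expects the findings to inform public budgets and commissioning. A null result could be read as no effect of homecare on health service demand, or a favourable one as a saving, when either may partly reflect who was left to survey. An analysis plan cannot recover the missing people from data on respondents alone.

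**Working it through.** **1. Does any described source recover the lost admissions?**

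- Unpaid carers enter only through a participating care recipient (Inclusion criteria), so they cannot report on people who have died or left.
- The care-home data are a separate existing dataset of about 679 residents in 34 homes (Data requirements), not this study's clients followed into care homes.
- Hospital records linked for respondents only would have the same gap.
- The limitations in the Discussion cover sample size, instrument sensitivity and functional form, not this exit.

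**2. Do the planned methods deal with it?** The instrument is the leave-one-out average of formal care in the local area. It addresses why people receive different amounts of care. If local provision also affects who returns home after an admission, the instrument is itself related to being in the sample. Matching balances observed characteristics among those sampled and has no data on leavers.

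**3. How large could the bias be?** The article gives no figure for hospitalisations to reproduce; its sample-size figures concern quality of life and do not bear on this point. All rates below are assumptions.

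Let p be the true admission risk, r the share of admitted people back in the sampled population at the survey, and s the share of non-admitted people still in it. Then

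observed admission = p·r / [p·r + (1 − p)·s].

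The observed odds are p·r / [(1 − p)·s], so

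observed odds ratio (high v low care) = true odds ratio × (r_high / r_low) × (s_low / s_high).

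If r and s are each equal across care levels, the odds ratio is unchanged.

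Take p = 20% under low care. Under high care take p = 20% (no true effect) or 16% (true ratio 0.80). For the first row, low care is 0.20×0.60 / (0.20×0.60 + 0.80×0.95) = 0.120/0.880 = 13.6%. High care with no effect is 0.160/0.920 = 17.4%, a ratio of 1.28. High care with p = 16% is 0.128/0.926 = 13.8%, a ratio of 1.01. The other rows follow in the same way.

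| r, low v high | s, low v high | Observed low | Observed high, no effect | Ratio, no effect | Ratio, true 0.80 |
|---|---|---|---|---|---|
| 60% v 80% | 95% v 95% | 13.6% | 17.4% | 1.28 | 1.01 |
| 70% v 80% | 95% v 95% | 15.6% | 17.4% | 1.12 | 0.89 |
| 70% v 80% | 85% v 95% | 17.1% | 17.4% | 1.02 | 0.81 |
| 70% v 70% | 95% v 95% | 15.6% | 15.6% | 1.00 | 0.79 |
| 80% v 60% | 95% v 95% | 17.4% | 13.6% | 0.78 | 0.62 |

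**4. The absolute difference.** Take a true risk of 30% under less care and 20% under more care (difference −10.0 points, odds ratio 0.58), with no exit among the non-admitted. Exit is 1 − r.

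| Exit after admission, less v more care | Observed risks | Difference, points | Odds ratio |
|---|---|---|---|
| 30% v 30% | 23.1% v 14.9% | −8.2 | 0.58 |
| 30% v 10% | 23.1% v 18.4% | −4.7 | 0.75 |
| 50% v 10% | 17.6% v 18.4% | +0.7 | 1.05 |
| 10% v 30% | 27.8% v 14.9% | −12.9 | 0.45 |

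Equal exit keeps the odds ratio but shrinks the absolute difference, which is the quantity that healthcare demand turns on. More exit under less care hides or reverses the effect; the opposite pattern exaggerates it.

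**The case against.** A reader might infer that the estimate is biased specifically against finding that care prevents admissions. The documents do not support that. They give no rates of death, return home or care-home moves by care level. More exit under less care is plausible but not shown; equal exit leaves the odds ratio intact, and the reverse pattern produces a spurious benefit. Exit without admission can also offset the bias: 70% v 80% return gives a null ratio of 1.12 with equal retention of the non-admitted, but 1.02 if that retention is 85% v 95%.

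A reader might also infer that long admissions are lost as such. They are lost only if the stay is still continuing at the survey or the person is no longer a client; someone back at home can report a long stay.

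It is also fair to say that the article does not state the look-back window, the data source or the definition of potentially avoidable. A condensed article may leave these to the full protocol. A short window would lose fewer people, and the exit rates assumed above are not tied to avoidable admissions in particular. The outcome has declared lower weight, and restriction to survivors is a familiar limit of cross-sectional surveys.

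These points remove any claim about direction or a specific size. They do not remove the gap: the article commits to effects on demand for healthcare, the sampled population excludes people whose admissions ended in exit, and no described method or data source addresses this.

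**Conclusion.** The point holds as a limit on what the hospitalisation analysis can conclude. As described, it concerns admissions among surviving current recipients of domiciliary care who can consent, not total healthcare demand. If exit after admission differs by care level, without a matching difference in exit among the non-admitted, the effect estimate is biased, with a direction that the documents do not fix. Under the assumed rates the null ratio ranges from 0.78 to 1.28, and a true ratio of 0.80 could appear anywhere from 0.62 to 1.01. These figures illustrate how sensitive the result is; they do not estimate the bias in this study. The matter deserves correction but concerns a secondary outcome. Nothing here bears on the primary analysis of the Adult Social Care Outcomes Toolkit.

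**What to change.** In Aims and objectives, Data requirements and Cost-effectiveness, define the outcome and the conclusion as potentially avoidable admissions among surviving current domiciliary care recipients, in place of total effects on healthcare demand. State the exit after admission as a limitation in the Discussion.

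Add one sensitivity analysis that varies both exit after admission and exit without admission by care level. Use a range stated in advance that runs in both directions, and report whether the sign of the effect survives. The formula above is sufficient for a simple version.

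The cost is a narrower claim on a secondary outcome and one extra analysis, with no new data collection. An aggregate count of clients who left through death, hospital or a care-home move could be requested from location managers as an option. The manager survey was scheduled for November 2025 to January 2026, so this may mean re-contacting about 150 locations and an ethics amendment. It would give no individual care hours and could not cover the 800 PA employers among the 1850 recipients.

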Survey packs to people accessing care via a care location and to people who are employing a PA will include (1) a cover letter/invitation email, (2) a participant information sheet for care recipients and one for unpaid carers, (3) the care recipient and unpaid carer questionnaires, (4) a study privacy notice and (5) two free post envelopes.

Participants will be offered the option to (1) complete a hardcopy (paper) version of the questionnaire (alone or with help), (2) complete an online version of the questionnaire (alone or with help) or (3) arrange a telephone or face-to-face interview. By providing a number of options, we are hoping to accommodate the participants’ needs and to be as inclusive as possible.

Care locations are offered financial compensation for participation in the study in accordance with the NIHR Schedule of Events Costing Attribution Tool. Also, care recipients and unpaid carers returning completed questionnaires will be offered high-street vouchers as a thank you. The value of high-street vouchers is based on NIHR guidance for payments to public contributors in research.

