### Sample size calculations

Sample sizes were determined using power calculations based on differences in means of ASCOT QoL scores between groups of LTC recipients, using Adult Social Care Survey (ASCS) 2021 data. Despite its limitations (eg, it does not include people self-funding their care and does not allow the identification of homecare recipients but only people accessing a broader range of community-based services), ASCS is the largest dataset capturing outcomes of people accessing LTC in England.

For the comparative analysis between people accessing homecare and care home residents, we would expect a difference in QoL scores of <0.1 (on a scale from 0 to 1). For detecting a statistically significant difference in QoL of 0.05 and considering an SD of QoL scores of 0.189, power calculations with alpha of 0.05 and power of 80% show that we would need a minimum sample of 226 observations in each group. The comparative cost-effectiveness analysis with care home residents will need to include homecare recipients with higher levels of care needs (ie, equivalent to care needs of care home residents). Allowing for three levels of care needs for the homecare recipients group (ie, low, medium and high) and taking into account that we will not be able to control during fieldwork how many respondents will be in each care need subgroup, we rounded up the target sample of homecare recipients to 800.

For the comparative analysis between homecare agency clients and PA employers, we expect a difference in QoL of 0.02 to 0.03. For detecting a statistically significant difference in QoL and considering an SD of QoL scores of 0.188, power calculations with an alpha of 0.05 and power of 80% show that we would need a sample of between 616 and 1389 observations in each group. To avoid setting unrealistically high target samples (and increasing research costs), we aim for a similar sample of 800 PA employers, as determined in the previous step for homecare agency clients.

The very limited information on care outcomes of housing with care residents is from findings of the Adult Social Services Environments and Settings (ASSET) and the Outcomes of Social Care for Adults (OSCA) studies, which found QoL scores of around 0.90. We based the power calculation (with an alpha of 0.05 and power of 80%) on an expected difference in QoL of 0.05 and SD of 0.189, leading to a minimum sample of 226 housing with care residents, which we rounded up to 250.

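### In the homecare-versus-care-home comparison, self-reported and proxy-reported QoL are fully confounded with setting, so the matched setting effect absorbs any rater offset

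*Protocol article*

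**What the plan says.** **Homecare side.** Under Data requirements, the primary outcome "for people accessing care and for their unpaid carers is the ASCOT interview version", that is, ASCOT-INT4. Under Recruitment of study participants, care recipients may "complete a hardcopy (paper) version of the questionnaire (alone or with help"), do the same online, or be interviewed by telephone or face to face. No proxy version is named for them.

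**Care-home side.** No new data are collected. Under Data requirements the comparator is the DACHA dataset, with residents' "QoL (collected using ASCOT Proxy") and a stated size: "The dataset includes a sample of about 679 residents from 34 care homes in England". The same paragraph says that the new questionnaires were designed with that dataset's structure in mind, so that the two sources can be compared.

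**Capacity.** Under Inclusion criteria, "All participants must have the mental capacity to consent", and for provider-recruited clients "we will instruct care providers to exclude people who lack the mental capacity to consent". The article describes no corresponding rule for the care-home residents.

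**Analysis.** Under Data analysis, comparisons between settings rely on matching on observed characteristics; the examples given are demographic factors, health issues and ADL difficulty. Under Cost-effectiveness, the coefficient of the binary setting variable is read as the average treatment effect on the treated (ATT). Under Sample size calculations, this comparison is powered "For detecting a statistically significant difference in QoL of 0.05" with SD 0.189, and the expected difference is below 0.1.

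**The concern.** Every care-home score is a proxy rating and every homecare score is given by the care recipient. If proxies rate systematically higher or lower than people rate themselves, that gap looks exactly like a difference between settings. No matching variable can separate the two, because neither rater nor instrument version overlaps between the arms. The identifying condition given under Data analysis (assignment to groups random given the controls) concerns selection into settings. It does not cover an outcome that is measured differently in each arm.

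The population difference adds to this. The homecare sample contains nobody judged to lack capacity, so any care-home residents without capacity would have no like-for-like match. The restriction on the homecare side under Sample size calculations is by level of care need, which is not the same thing as capacity.

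The plan's other safeguards do not reach this comparison. The instrumental-variable analysis addresses care intensity. The self-estimated gain needs the expected-QoL questions of ASCOT-INT4, which the article does not show to be available in the proxy data. Neither the rater difference nor the capacity difference appears among the stated limitations. At stake is how homecare and care homes compare on value for money, a result intended for commissioners and budget setters.

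**Working it through.** **Inputs from the article (Sample size calculations, Data requirements).** Target difference 0.05; SD 0.189; alpha 0.05; power 80%; 226 per group; 800 homecare clients across three need levels; about 679 residents in 34 homes.

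**Assumed here.** A two-sided test, since sidedness is not stated. A constant offset b between self-report and proxy report, for which the article gives no value; the range shown is 0.01 to 0.05. For the second scenario, one third of 800, about 267 clients, with high needs.

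**Step 1: the plan's own figure.**
- Normal approximation: n = 2 × (1.960 + 0.842)² × 0.189² / 0.05² ≈ 224.3, rounded up to 225 per group.
- The two-sample t-test solution is 225.26, rounded up to 226.
- The stated 226 reproduces. The sample-size arithmetic is sound; the issue is bias.

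**Step 2: how an offset enters.** Observed difference = true setting effect + b. Since b is the same for every pair whatever it is matched on, matched coefficient = ATT + b.

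**Step 3: standard errors, ignoring clustering and matching losses.** SE = 0.189 × √(1/n₁ + 1/n₂).
- 226 v 226: SE = 0.0178.
- 267 v 679: SE = 0.0137.

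**Step 4: probability of a significant result with no true setting effect.** P = Φ(b/SE − 1.96) + Φ(−b/SE − 1.96).

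| Assumed offset b | 226 v 226 | 267 v 679 |
|---|---|---|
| 0 | 5% | 5% |
| 0.01 | 9% | 11% |
| 0.02 | 20% | 31% |
| 0.03 | 39% | 59% |
| 0.05 | 80% | 96% |

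The larger sample makes the false-positive rate higher, because it estimates the wrong quantity more precisely.

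**Step 5: offset against a real effect.** If the true effect is 0.05 and the offset is 0.05 in the opposite direction, the expected difference is 0. A significant result in the right direction then occurs about 2.5% of the time, against 80% (226 v 226) or 96% (267 v 679) without the offset.

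**Step 6: cost-effectiveness, as an illustration.** For a fixed cost difference, the ratio varies as 1/(QoL difference). With a true difference of 0.05, an offset of +0.02 gives 0.07 and multiplies the ratio by 0.05/0.07 = 0.71. An offset of −0.02 gives 0.03 and multiplies it by 0.05/0.03 = 1.67.

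**Step 7: a rough allowance for clustering.** There are 679/34 ≈ 20 residents per home. With an assumed ICC of 0.05 on the care-home side only, the design effect is 1 + 19 × 0.05 ≈ 1.95, and SE = 0.189 × √(1/267 + 1.95/679) ≈ 0.0154. The 267 v 679 figures for offsets of 0.03 and 0.05 fall to about 50% and 90%. The bias itself stays at b.

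**The case against.** **The offset is assumed.** The article gives no self-minus-proxy gap, and setting it equal to the target difference simply returns the power of the test. The 267 also rests on equal thirds, although the article says subgroup numbers cannot be controlled. This stands: the table shows sensitivity and does not predict a result. The confounding itself needs no assumption.

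**The covariate list is only illustrative.** It is given as examples, health issues could capture diagnosed cognitive impairment in part, and the final matching set may be fixed elsewhere. This also stands, so the absence of cognition from the list is not itself a fault. No covariate list, however, could remove the rater difference.

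**Residents without capacity.** A reader might infer that the care-home data were collected with no capacity filter, or that residents' needs are largely cognitive. The article supports neither. It does not describe that dataset's eligibility rules, and silence does not show that no rule was applied.

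**Alignment.** A reader might infer that the article claims equivalent measurement in the two sources. It says only that questionnaire design was informed by the other dataset, and it discloses the proxy instrument openly.

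**Estimand.** If homecare is the treated group, the ATT already describes people with capacity. That is fair, but the article does not fix which group is treated. Even then, residents without capacity could serve as matches unless capacity or cognition is used in the matching.

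**Help with completion.** Some homecare clients will answer with help, which may narrow the gap between raters. It does not turn ASCOT-INT4 into a proxy rating.

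**Conclusion.** The concern holds for the homecare-versus-care-home comparison. Instrument and rater coincide completely with setting, the planned matching cannot separate them, and any offset enters the ATT one-for-one. For assumed offsets of 0.02 to 0.05 with no true effect, the false-positive rate is about 20% to 80% at the plan's 226 per group, and 31% to 96% at an assumed 267 v 679. These figures assume a constant offset, SD 0.189 in both groups, and no clustering or matching losses. The documents give neither the size nor the direction of the offset, so the bias could create, inflate or hide a setting effect. The capacity point is secondary and conditional: no filter is described for the residents, so comparability on capacity is not established.

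A reader might infer that the study as a whole is undermined. It is not. The Discussion places the main question on QoL gain per additional unit of care. The instrumental-variable analysis of care intensity and the comparisons within domiciliary care do not depend on the proxy data. This should be fixed, but it affects one of several comparisons.

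**What to change.** For this comparison only:

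1. Pre-specify re-estimation of the ATT and of the cost-effectiveness result over a grid of self-minus-proxy offsets. Report the offset at which the conclusion changes, and present the comparison as conditional on that offset, not as a clean setting effect. State before analysis which offsets are regarded as plausible and why. The whole expected difference is below 0.1, so a very wide grid with no such statement would overturn almost any result and inform nobody.
2. Where the care-home dataset records capacity or cognition, restrict or match on it, trim to common support, and state that the result applies to people with capacity. If it records neither, say so.
3. List the instrument and rater difference among the limitations.

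Proxy questions put to the roughly 400 unpaid carers should not be relied on to measure the offset directly. The article does not say who the care-home proxies were, and the carers would be rating only people with capacity.

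The cost is analysis wording and a sensitivity table; no new data are needed. The downside is fewer usable care-home residents and a more cautious conclusion.
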